### Outcome measures

Outcomes will be collected at baseline, the middle of treatment, after treatment, and follow-up 6 months after the completion of the treatment. The overview of the outcome measurement at the different time points is shown in Table 3.

**Table 3 Tab3:** Overview of study visits

		Study period						
		Enrollment	Allocation	Post allocation			Close out	Follow-up
	Time point (month)	− 1	0	1	2	3		6
Preparation	Enrollment							
	Informed consent	√						
	Eligibility screen	√						
	Allocation		√					
Intervention	OA			√	√	√		
	SA			√	√	√		
Assessment	Liver function Kidney function	√						
	T; BP; P; R	√		√	√	√		
	BMD	√						√
	E2; FSH	√						
	BGP; BALP	√						
	TAC; AOPP	√						
	FoxO3a; β-catenin PPARγ	√						
	VAS	√		√	√	√		√
	TCM syndrome	√			√			
	QOL	√			√			
	Adverse events						√	
	Data analysis						√	
	Fracture rate							√

*T* body temperature, *BP* blood pressure, *P* pulse rate, *R* respiration rate, *OA*, *SA*, *QOL* quality of life, *TCM* traditional Chinese Medicine, *VAS* visual analog scale, *PPAR*, *E2*, *TAC*, *AOPP*, *BGP*, *BALP*, *BMD*, *FSH*

### Primary outcome

The primary outcome is BMD. BMD is measured using dual-energy x-ray (DEXA) absorptiometry (DMS, Paris, France; model: CHALLENGER C 313). A BMD measurement of the lumbar vertebrae (L1–L4) in the two groups will be measured before and after treatment.

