**Methods/design:**

This study is a randomized, sham-controlled, patient- and assessor-blinded trial and aims to evaluate the effect of OA in women with PMOP. We will recruit 104 women aged 45–70 years with a diagnosis of PMOP. Participants will be randomly allocated in a 1:1 ratio to the OA group and the sham acupuncture (SA) group. Both groups will receive real herbal medicine treatment as a basic treatment twice a day for 3 months, the OA group receives real acupuncture treatment and the SA group receives placebo acupuncture treatment (non-penetrating, sham skin-needle therapy, sham cupping). All patients will receive acupuncture treatment twice per week for 3 months. The primary outcome is bone mineral density (BMD) and the secondary outcomes include estradiol (E2), follicle-stimulating hormone (FSH), bone gla protein (BGP), bone alkaline phosphatase (BALP), total antioxidant capacity (TAC), advanced oxidation protein products (AOPP), PPARγ, β-catenin, FoxO3a levels, visual analog pain scale score (VAS), Traditional Chinese medicine (TCM) syndrome scores and quality of daily life score (QOL). Outcome measures will be collected at baseline, middle of the treatment (1.5 months), the end of treatment (3 months). The present protocol followed the SPIRIT guidelines and fulfills the SPIRIT Checklist.

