### Interventions

Both the OA and SA groups will receive acupuncture sessions for a total of 3 months. All the patients will receive herbal medicine twice a day for 3 months. The same physician (the Professor of Acupuncture in Yunnan Provincial Hospital and Traditional Chinese Medicine, who has 20 years of work experience) will slightly adjust the formula each week depending on the changes of the symptoms, pulse, and tongue coating of the patients (main herbal formula components are shown in Table 1). During the trial, patients will be classified by pattern differentiation: (1) spleen-kidney *Yang* deficiency will be given Yougui Pill; (2) liver-kidney *Yin* deficiency will be given Zuogui Pill; and (3) kidney deficiency and blood stasis will be given Bushen Huoxue decoction. Participants will be given all the herbs from the same hospital and the physician will instruct them how to decoct.

**Table 1 Tab1:** Main herbal formula selection

Pattern	Formula	Composition
Spleen-kidney *Yang* deficiency	Yougui Pill	radix rehmanniae preparata, cortex cinnamomi, cornu cervi degelatinatum, rhizoma dioscoreae, fructus corni, fructus lycii, radix angelicae sinensis, cortex eucommiae, semen cuscutae, radix morindae officinalis, rhizoma drynaria, rhizoma sparganii
Spleen-kidney *Yin* deficiency	Zuogui Pill	radix rehmanniae preparata, rhizoma dioscoreae, fructus lycii, fructus corni, radix achyranthis bidentatae, deerhorn glue, deerhorn glue, radix morindae officinalis
Kidney deficiency and blood stasis	Bushen Huoxue decoction	radix rehmanniae preparata, semen cuscutae, cortex eucommiae, fructus lycii, radix angelicae sinensis, fructus corni, cistanches herba, commiphora myrrha, radix angelicae biseratae, radix angelicae sinensis

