### Blood testing

Sex hormones. Fasting blood samples will be draw every month before and after treatment by the nurse. Chemiluminescence immunoassay (CLIA) will be used to determine serum sex-hormone levels include estradiol (E2), FSH (Model: Berne, Switzerland, ELECSYS2011).Antioxidant index. Before and after intervention, a 5-ml venous blood sample will be obtained under non-fasting conditions. Samples will be frozen at − 70 °C. Advanced oxidation protein products (AOPP), and total antioxidant capacity (TAC) (with 2,2-diphenyl-1-picrylhydrazyl (DPPH) oxidation) will be measured using the following methods: Walwadkar [18], Kataaha et al. [19], Girbal et al. [20], Kitajima [21] and Janaszewska et al. [22].Bone metabolism index. Fasting venous blood will be collected before treatment, one course of treatment and at the end of treatment, respectively. The enzyme-linked immunosorbent assay (ELISA) (biocell enzyme standard instrument) will be used to determine bone gla protein (BGP) and bone alkaline phosphatase (BALP) before and after treatmentPathway signaling proteins. Western blot will be used to detect the expression of β-catenin, FoxO3a and PPARγ2 protein in bone tissue (Multiskan spectrum, Shanghai, China, ThermoScientific, USA).Follow-up is at 6 months after the completion of the treatment. Follow-up will be performed by telephone to ask if the participants have sustained any new fracture or have experienced recurrence of pain.

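### The post-baseline time of the primary BMD scan is contradictory: the text points to end of treatment (month 3), while Table 3 ticks BMD only at enrolment and follow-up

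*Protocol article*

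**What the plan says.** The Primary outcome section defines the endpoint as L1–L4 BMD by dual-energy x-ray absorptiometry, which "in the two groups will be measured before and after treatment". It gives no month. The month comes from two other places. The Interventions section states that "Both the OA and SA groups will receive acupuncture sessions for a total of 3 months". The abstract's Methods/design paragraph states: "Outcome measures will be collected at baseline, middle of the treatment (1.5 months), the end of treatment (3 months", and lists no later collection.

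The Outcome measures section is broader: "Outcomes will be collected at baseline, the middle of treatment, after treatment, and follow-up 6 months after the completion of the treatment". It then refers to Table 3 ("Overview of study visits"), where the BMD row has two ticks, at enrolment (month −1) and in the follow-up column headed 6.

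The end of the Blood testing section describes the follow-up contact: "Follow-up will be performed by telephone to ask if the participants have sustained any new fracture", or a return of pain. It mentions no clinic attendance at that point.

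**The concern.** The article places the one measurement on which the trial will be judged in two ways. Staff commonly work from the schedule table, and this table has no BMD scan at the end of treatment. A scan taken only at follow-up would show whether any difference persists after treatment has stopped. A scan at month 3 would show whether the treatment produced a difference while it was given. These are separate questions and need not have the same answer.

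The missing-data rule adds to the risk. The Data analysis section carries the last observation forward. For a participant with no scan at month 3, the only earlier BMD value is the baseline one, so carrying it forward would record a change of zero.

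**Working it through.** The plan gives no figure to reproduce here, and the sample-size calculation plays no part. The check sets the statements side by side and reads Table 3 cell by cell.

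1. **Time implied by the text.** The Primary outcome section asks for a scan after treatment, the Interventions section gives a 3-month treatment, and the abstract equates end of treatment with 3 months. Together these put the post-baseline scan at month 3.

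2. **Time in Table 3.** The seven time columns are −1, 0, 1, 2, 3, close-out (no month given) and 6 (follow-up). The BMD row is: tick, blank, blank, blank, blank, blank, tick. The ticks fall in the first and seventh columns, month −1 and follow-up (6). Month 3 and close-out are blank.

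3. **Could the tick have shifted when the table was read from PDF?** This cannot be wholly excluded, but it is unlikely. The BMD row has as many cells as the header. The VAS row has separate ticks at months 1, 2, 3 and follow-up. The OA, SA and vital-sign rows also use month 3, so that column was not lost. The second BMD tick shares its column with the fracture-rate tick, and fracture is what the telephone call asks about.

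4. **How the follow-up is done.** BMD needs an attended scan. The article describes the follow-up as a telephone call and mentions no visit at which the Table 3 scan could be taken.

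5. **When the follow-up is.** On Table 3's month axis it is month 6, which is 6 − 3 = 3 months after treatment ends. The Outcome measures section says "follow-up 6 months after the completion of the treatment", and the Blood testing section says the same; counted from allocation, that contact falls at 3 + 6 = month 9. The label is therefore ambiguous about its origin.

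6. **Other rows of Table 3 against the text.**
   - Estradiol and FSH: enrolment only in Table 3. Blood testing says "Fasting blood samples will be draw every month before and after treatment by the nurse".
   - Antioxidant indices (TAC, AOPP) and bone markers (BGP, BALP): enrolment only in Table 3. Blood testing plans post-intervention antioxidant samples and end-of-treatment bone markers.
   - Liver and kidney function: enrolment only in Table 3. The Adverse events section repeats them after 12 weeks of treatment.
   - TCM syndrome and QOL scores: enrolment and month 2 in Table 3. The text scores the TCM syndrome weekly, and the forms in Tables 5 and 6 both have a post-treatment entry.
   - Mid-treatment visit: 1.5 months in the abstract. Table 3 has months 1, 2 and 3 and no 1.5-month column.

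**The case against.** The best defence is that the text is clear enough. The Primary outcome section and the abstract both plan a post-treatment measurement, the Blood testing section plans post-treatment samples, and a table in a condensed article may simply have lost ticks. That several laboratory rows have one tick against explicit text gives this some weight, most of all for those secondary rows. It does not remove the problem for BMD. That row has a post-baseline tick, and it is in a different place from the one the text implies. The article does not say which governs.

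Four stronger readings are tempting, and the documents do not support them.

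- A reader might infer that no participant at all would have a post-baseline BMD or blood result. That takes the missing month-3 tick from Table 3 but rejects the table's own follow-up tick because of the telephone text. It also ignores the post-treatment scan and bloods that the text plans. Neither source, followed consistently, gives zero BMD data.
- A reader might count three candidate times for the primary scan: months 3, 6 and 9. No sentence specifically places BMD at month 9. The 6 in Table 3 sits under a separate follow-up heading after an undated close-out, so it may mean six months of follow-up, in line with the Discussion. BMD has two placements, and the calendar date of the second is unclear.
- A reader might say that a follow-up scan is impossible. The Blood testing section says what the call is for; it does not exclude attendance for a scan. The gap is that no attended visit is described.
- A reader might say that the Primary outcome section itself fixes month 3. It names no month. The month comes from the abstract and the treatment duration.

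The worry that the time point could be picked after seeing results is also limited. It would need scans at two post-baseline times, and only the general sentence in Outcome measures could imply that.

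**Conclusion.** The contradiction is real, concerns the primary endpoint and must be resolved. The text, read as a whole, supports month 3. Table 3 leaves month 3 empty and puts the only post-baseline BMD in a follow-up column whose origin is unclear and whose only described contact is by telephone. The consequence is conditional: a site that follows Table 3 omits the end-of-treatment scan, and any later scan measures an off-treatment effect. The documents do not say which source sites follow, so no count of affected participants can be given.

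The conclusion assumes that the Table 3 ticks were read in their true columns, which the cell count and neighbouring rows support. The ambiguous follow-up label, and the abstract's 1.5-month collection with no matching column, do not depend on where the BMD tick falls. The disagreements on bloods, safety tests and scores show that the table needs a full reconciliation, but they are secondary to the BMD row.

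**What to change.** - Name one primary time point: L1–L4 BMD at the end of treatment (month 3), which is what the abstract, the Interventions section and the Primary outcome section jointly support.
- Correct the BMD row of Table 3 to show it. Either remove the follow-up BMD tick, or keep it, label it secondary and state that the visit is in person.
- Give one follow-up time with a named origin (allocation or end of treatment), and use it in Table 3, Outcome measures and Blood testing.
- Reconcile the remaining rows with the text: hormones, antioxidant indices, bone markers, liver and kidney tests, TCM and QOL scores, and the 1.5-month visit against the month-1 and month-2 columns.

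The cost is an amended table, a few sentences and notification. The Study design section requires changes to go to all researchers, the Ethics Committees and the registry. Recruitment had started on 1 August 2018, with the last inclusion expected on 1 August 2020, so sites already enrolling would need the corrected schedule. No new procedure is needed, because the text already plans the post-treatment measurements.

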### Secondary outcomes

#### Pain score

The pain score will be assessed for the lower back. A visual analogue scale (VAS) will be used to measure each group before and after treatment (see attached Table 4).

**Table 4 Tab4:**
[figure not shown]
Visual analog scale (VAS)

Note: the visual analog scale is a line 10 cm long with a scale of 0–10, in which 0 denotes no pain and 10 denotes the worst pain. Patients are asked to mark their pains on the line, and the examiner scores the VAS by measuring the distance in centimeters (0 to 10) from 0 to the mark

The TCM syndrome scores will be recorded by the same professor once a week to adjust the acupuncture and herbal treatment [17] and evaluate the improvement of the patients’ TCM syndromes (see attached Table 5).

**Table 5 Tab5:** Osteoporosis symptom grading scale (points)

Symptoms	None (0 points)	Mild (2 points)	Moderate (4 points)	Severe (6 points)
**Low-back pain**	**None**	**1–3°**	**4–6°**	**7–9°**
**Soreness and wea kness of waist and knees**	**None**	**After overwalking, I feel a little sore in my waist and knees**	**Somewhere in between**	**Soreness and wea kness of waist and knees continue to occur, and I do not want to stand and****walk**
**Lower limb pain**	**None**	**1–3°**	**4–6°**	**7–9°**
**Impotence and weakness in the lower limbs**	**None**	**After walking(≥ 1 km) I may have sore lower limbs****occasionally**	**After walking** **(300 m–1 km) I may feel weak and sore in my lower limbs**	**After standing and walking (< 300 m) My legs may immediately feel tired**
**Difficulty in walking**	**None**	**It is inconvenient for me to walk occasionally, and I do not feel discomfort walking less than 100 m**	**It is difficult for me to walk even for a short distance (10–100 m)**	**It is difficult for me to stand and walk. And I cannot walk for more than 10 m**
**Dizziness**	**None**	**I get dizzy occasionally, but dizziness does not affect my daily life**	**I get dizzy sometimes, and dizziness would get worse when I am tired, which affects my daily life**	**I get dizzy when I move, and sometimes even fall down, which seriously affects my daily life**

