### Sample size and blinding

According to the preliminary research [15], we hypothesize that the effective rate after OA is 77.8% and the effective rate after SA is 50%. The equation that we used for this was *α* = 0.05, *β* = 0.20 and we determined that a sample size of 42 patients in each group would be sufficient to detect the statistical difference between the two groups, allowing for a 20% withdrawal rate. We will plan to enroll a total of 104 participants with 52 participants in each group. According to the random number sequence generated by computer, the patients will be randomly divided into either the OA group or the SA group in a 1:1 ratio.

The participants, outcome assessors, study monitors, data managers, and statisticians will be blinded to treatment allocation. If possible, the study participants will be advised to avoid discussing the investigational treatments with other participants. Blinding will be maintained until the 104 participants have completed the study. The success of double-blinding will be assessed at the final visit. Due to the special nature of acupuncture, acupuncturists cannot be blinded to the treatment. The database will then be locked. An emergency code for each individual has been provided to the study researchers and will be disclosed only if it must be known whether a patient is receiving acupuncture treatment or SA in order to manage a serious adverse event.

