According to the OA and moxibustion [15], and taking opinions from Chinese acupuncture experts, the essential acupuncture points selected are as follows: BL11 (Dazhu), BL23 (Shenshu) and ST36 (Zusanli). The additional individualized acupuncture points will be chosen by the practitioners according to the patterns of identification: (1) kidney *Yang* deficiency will have added DU04 (Mingmen), GB34 (Guanyuan); (2) spleen-kidney *Yang* deficiency will have added DU04 (Mingmen), GB34 (Guanyuan); (2) liver-kidney *Yin* deficiency will have added SP06 (Sanyinjiao), LU11 (Taixi); (3) kidney deficiency and blood stasis will have added SP06 (Sanyinjiao), BL17 (Geshu) (Table 2). A placebo device [16] will be applied in both groups for better implementation of blinding. The schematic diagram of the acupuncture treatment is shown in Fig. 2.The acupuncture treatment in both groups will take 30 min per session, twice per week. Three months is the duration of a course of treatment, for a total of one course .

**Table 2 Tab2:** Acupuncture point selection

Point	Location
BL11 (Dazhu)	In the spinal region, under the spinous process of the 1st thoracic vertebra, 1.5 cun lateral to the posterior midline
BL23 (Shenshu)	1.5 cun beside the spinous process of the 2nd lumbar vertebra
ST36 (Zusanli)	At the anterior aspect of the leg 3 cun inferior to ST35 (Dubi) on the line connecting ST35 (Dubi) to ST41 (Jiexi)
DU04 (Mingmen)	Between the spinous processes of the 2nd and 3rd lumbar vertebrae
GB34 (Guanyuan)	On the lower abdomen at the anterior midline, 3 cun below the umbilicus
SP06 (Sanyinjiao)	On the tibial aspect of the leg posterior to the medial border of the tibia, 3 cun superior to the prominence of the medial malleolus
LU11 (Taixi)	On the posteromedial aspect of the ankle in the depression between the prominence of the medial malleolus and the calcaneal tendon
BL17 (Geshu)	Under the spinous process of the 7th thoracic spine on the back, 1.5 cun lateral to the midline

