### Overall adjustment acupuncture (OA) group

Acupuncture manipulation will be applied to the acupoints of the body until the patient achieves *Qi*, including soreness, soreness and distension, pain, numbness, tingling and even comfort. Huatuo brand needles (0.25 mm × 40 mm) are manufactured by the Suzhou Medical Device Company in Suzhou, Jiangsu Province, China. After the patient achieves *Qi* in Shenshu and Zusanli, warm acupuncture will be used, the 2 cm-long moxa-stick will be fixed on the handle of the needle and lit at the root of the needle and allowed to burn for 20 min.

The parameters of the skin-needle are set as follows: *Qixing* needle; tapping along the first side line of the urinary bladder meridian in the back; moderate stimulation will be applied for blood stasis and *Qi* stagnation type, until redness of the skin and petechiae are observed in the tapping area; mild stimulation is used for the other syndromes until redness in the skin is observed.

The parameters of the cupping are set as follows: moving cupping; smear the tapping spot evenly with Vaseline and move the cup along the first lateral line of the urinary bladder meridian, back and forth until red-blood stasis appears on the skin, according to the patient’s tolerance (feeling comfortable, without obvious pain). Retaining cupping: leave the cup for 8 to 10 min in Dazhui, Shenshu, and a severely painful area.

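### The TCM syndrome score, a secondary outcome, is recorded by the professor who uses it to adjust treatment, so the claim of blinded outcome assessors is not secured for it

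*Protocol article*

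**What the plan says.** The Abstract (Methods/design) names TCM syndrome scores among the secondary outcomes. The Secondary outcomes section, below Table 4, says who scores them and why: "The TCM syndrome scores will be recorded by the same professor once a week to adjust the acupuncture and herbal treatment". The same sentence adds a second purpose, to "evaluate the improvement of the patients’ TCM syndromes". One person's weekly score therefore serves both as a treatment-adjustment tool and as an efficacy measure.

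The Interventions section describes the herbal background treatment, which both arms receive. One physician, the Professor of Acupuncture at one of the two hospitals, "will slightly adjust the formula each week depending on the changes of the symptoms, pulse, and tongue coating of the patients". The same section gives the choice of individualized points to the treating side: "The additional individualized acupuncture points will be chosen by the practitioners according to the patterns of identification".

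On blinding, Study design calls the trial patient- and assessor-blinded. Sample size and blinding states: "The participants, outcome assessors, study monitors, data managers, and statisticians will be blinded to treatment allocation". It makes no exception for any outcome. It also concedes that "acupuncturists cannot be blinded to the treatment".

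In the OA group section, moving cupping continues "until red-blood stasis appears on the skin". The sham section has cotton-wrapped skin needles, no skin penetration and less suction than in the OA arm.

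**The concern.** A blinded-assessor claim needs raters who are kept apart from treatment. For this outcome the protocol names a rater whose stated task includes adjusting the acupuncture and the herbs, and it says nothing about how that person is kept unaware of the arm. Followed as written, the rater of a listed outcome is also a director of treatment.

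Two things are at stake. The first is the TCM score itself. If the professor knows or guesses the arm, the grading could lean toward OA, and the trial would still report the result as assessor-blinded. The second is the herbal co-intervention. It is meant to be common to both arms, but it is changed weekly at the discretion of the same person. If those changes differed by arm, the comparison of OA with sham would no longer isolate the acupuncture.

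**Working it through.** **Roles side by side.** The plan has no figure of its own to reproduce here, so the main check is a reading of roles.

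1. The score is an outcome (Abstract; Secondary outcomes).
2. The scorer is one professor, weekly, who adjusts both acupuncture and herbs (Secondary outcomes). The Interventions section describes the weekly herbal prescriber as the Professor of Acupuncture, which fits the same person.
3. Adjusting acupuncture is a treating-side task (Interventions), and acupuncturists are declared unblindable (Sample size and blinding).
4. Outcome assessors are declared blinded, without exception (Study design; Sample size and blinding).
5. No section separates the scorer from the treating side or describes masking of that person.

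Items 2, 3 and 4 cannot be taken together as they stand unless masking of the professor is added.

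**Possible cues.** In the OA arm, cupping is continued until it marks the skin, for all participants. Skin-needling goes to petechiae only in the blood stasis and *Qi* stagnation type, and to redness in the other syndromes. Sham cupping uses less negative pressure. The marks are on the back.

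**Sensitivity of the score (illustration only).** Inputs:
- Table 5 has 6 items graded 0, 2, 4 or 6, so the maximum is 6 × 6 = 36 and one grade is 2 points.
- n = 42 per arm comes from Sample size and blinding.
- The SD is not given in the documents. I assume 4 to 8.
- I assume no true effect and a two-sample t-test at two-sided 5%, with 82 degrees of freedom and critical value 1.989.

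Formulas: d = shift / SD; noncentrality = d × √(n/2) = d × √21 = d × 4.583. The rejection rate is the two-sided power of the t-test at that noncentrality.

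| Average shift in OA | SD | d | Noncentrality | Rejection rate |
|---|---|---|---|---|
| 2 points (every OA participant one grade better on one item) | 8 | 0.25 | 1.146 | about 20% |
| 2 points | 4 | 0.50 | 2.291 | about 62% |
| 1 point (half the OA participants affected) | 8 | 0.125 | 0.573 | about 9% |
| 1 point | 4 | 0.25 | 1.146 | about 20% |

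The nominal rate is 5%.

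**Visit schedule.** The places that time this outcome disagree. The Abstract has baseline, 1.5 months and 3 months. Table 3, as it reads in the text available, marks TCM syndrome at enrollment and month 2. The Secondary outcomes text has weekly scoring. The Table 5 form has one pre-treatment and one post-treatment row.

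**The case against.** A reader might infer that the professor is unblinded, so that the protocol flatly contradicts itself. The documents do not support that. Only acupuncturists are named as unblindable, and Practitioner background describes those who deliver OA and sham separately from the prescribing professor. Points and herbs are chosen by TCM pattern, and the sham procedure is the same as OA apart from the devices, stimulation and suction. A prescriber could in principle adjust both without knowing the arm. This stands, and it limits the point to masking that is neither described nor safe to assume.

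A reader might also infer that the skin marks reveal the arm. Petechiae apply to one syndrome type only, and no section says the professor inspects the back. Herbal adjustment rests on symptoms, pulse and tongue. Sham cupping also applies some suction, and nothing says that it leaves no marks. The cupping marks are a possible cue and not proof of unblinding.

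Many Table 5 anchors are patient statements or walking distances, and participants are declared blinded. That narrows the rater's discretion but does not remove it: one moderate grade is defined only as lying between its neighbours.

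The 62% figure needs a full one-grade shift in every OA participant, none in the sham arm, and the smallest assumed SD. It shows sensitivity and predicts nothing.

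Finally, a reader might extend the concern to the primary outcome. BMD is measured by DXA and not rated by the professor, and the herbal changes are described as slight. An indirect effect through herbs adjusted differently by arm is possible, but the documents give nothing from which to size it.

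The article's brevity does not dispose of the point. It states who scores, how often and why, and it separately claims blinded assessment. The issue lies in what is stated.

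**Conclusion.** The point holds in a limited form. For the TCM syndrome score, the blinded-assessor claim is not secured, because the named rater uses the score to direct treatment and no masking is described. The score could be biased toward OA. Neither the professor's knowledge of allocation nor an actual bias is established.

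The illustrative false-positive rates are about 20% to 62% for an average 2-point shift, and about 9% to 20% for a 1-point shift. They rest on an assumed SD of 4 to 8, 42 analysed per arm, no true effect and a t-test.

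The scope is one secondary outcome and the comparability of the herbal co-intervention. The primary analysis is not shown to be affected.

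**What to change.** 1. For the outcome analysis, use TCM scores taken at baseline and end of treatment by the blinded outcome assessors the plan already declares. This matches the two rows on the Table 5 form.
2. Use the professor's weekly scores for treatment adjustment only, and say so in Secondary outcomes.
3. Reconcile the timing of this outcome across the Abstract, Table 3 and the Secondary outcomes text.
4. Tabulate herbal formula changes by arm, so that any divergence in the co-intervention can be seen.
5. If blinded scoring cannot be arranged, state in Sample size and blinding that the TCM outcome is not assessor-blinded, and report it as descriptive.

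The cost is two assessments per participant moved to the declared assessors, plus one extra table. With 104 participants that is 2 × 104 = 208 assessments over two sites. The documents do not give the number of assessors at each site, so their availability should be confirmed. The fallback in item 5 costs a sentence and the inferential standing of this one outcome.
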